### **Procedure for adverse reactions treatment**

1. In case of severe AE the treatment is stopped and the patient is immediately withdrawn from the trial.
2. In case of death, this should be immediately informed to monitors and to the main investigator of study.
3. The hospital should guarantee all the conditions and medications to handle anaphylactic reactions if they appear.
4. Another type of AE will be treated in a symptomatic form according to the rules indicated at each service.

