#### Regarding adverse reactions

-It has been widely recognized the adverse reactions of interferon therapy, none of them have been associated until now to the use of any therapeutic vaccination under study, including NASVAC.

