### **3. Ethics and Medical Deontology**

#### **General ethical considerations**

The trial is justified from the ethical point of view because:

- The study is carried out according to the principles of the Declaration of Helsinki on investigations with human beings for therapeutics purposes. The patients will receive the medical care and the normal general treatment that is applied in these cases.
- CHB is a slow developing disease. The fact of being 6 – 12 months without any of the specific recognized treatments will not affect significantly the patients' evolution. Besides, follow-up will be very cautious and upon any sign of disease progression, the patient will be withdrawn from the study treatment and given a recognized specific anti-hepatitis therapy (interferon alpha or Lamivudine). In all cases patients included in the trial, after its completion will receive one of these treatments, if the principal patient and investigator decide.

- It is possible that the patients obtain benefit from their participation in the study since there are reasonable evidences that vaccination can improve their condition according to phase I results.
- Treatment of CHB patients with NASVAC, according to the results obtained at CIGB, does not represent additional risk for the patients. It is a quite safe intervention, with a very low probability of associated adverse reactions. Doctors can properly treat the possible adverse reactions and a favorable risk-benefit balance justifies them.
- Written consent of individuals will be requested, after properly informing about the objectives of the investigation, treatment to be subjected and possibility to refuse to participate in the trial at any moment without consequences to his medical care. When publishing, the confidentiality of the individuals' personal data will be guaranteed.
- All patients unable to satisfactorily control the viral load will be treated with available antiviral drugs, according to their physician decision, independently whether they belong to the control or treatment groups.
- There are preliminary evidences of safety and efficacy after the first clinical trial using NASVAC in chronic hepatitis B patients, conducted in Dhaka, Bangladesh, as previously described in the present protocol.

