### **5.5 Exit criteria or interruption of the treatment after inclusion**

- Voluntary abandonment of the patient.
- Appearance of any of the above-mentioned exclusion criteria.
- Patients with worsening of the liver pathology in comparison with baseline levels, according to the investigator's criteria.
- Severe adverse reactions according to WHO guidelines
- Feverish status (more than 37.8 °C) at the moment of vaccine administration or in the 24 hour before, or any suspected or confirmed infectious diseases that results in the suspension of three vaccine administrations during the course of the immunization schedule.
- Patient's death.

Patients, once included, will be considered in the analysis even if they interrupt the treatment. Therefore, no case report form will be eliminated.

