#### **Evaluation criteria regarding safety**

All AE that appear during the study will be recorded in the Case Report Form of each individual.

All medical incidents that occur in the first hour after each administration of the vaccine, causally related or not with the vaccination will be recorded.

The rest of the observations will be evaluated in the follow up visits every 14 days.

The observation includes medical questionnaire of the patient, inspection of the injection site, axillary's temperature, and registration of all symptoms and signs referred by the patient. Explanation of how to act in case of abandonment or exit in the trial

The patients that abandon the trial will always be evaluated, except if the investigator loses contact with him. The information will be registered in the Case Report Form (CRF), including the cause of exit.

Quality control of the evaluation procedure

The clinical and laboratory evaluations will be preserved, in order to be examined by external quality controllers.

All primary data should be collected and conserved during the study.

The frequency of specific determinations as well as the type of determination per specific date according to the protocol are presented below: (Grey boxes: Determinations will not be performed).

| Test                    | Baseline
(not more than 2 months before starting treatment) | Week 12 | Week 24
EOT-V | Week 36 | Week 48
EOT-I | Week 72 | Week 96 | Reference Values
(M: male, F: female) |
|-------------------------|----------------------------------------------------------------|---------|------------------|---------|------------------|---------|---------|------------------------------------------|
| Hemoglobin              |                                                                |         |                  |         |                  |         |         | M: 12-17 g/dL
F: 11.5-15.5 g/dL       |
| Hematocrit (PCV)        |                                                                |         |                  |         |                  |         |         | 37-54%                                   |
| Leukocytes              |                                                                |         |                  |         |                  |         |         | 4-10 x 10  /L                |

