## **8. Adverse reactions**

### **Adverse events that can be presented and methods to register them**

General AE described for the NASVAC TVC use are generally mild (**see the Reports of Phase I Clinical Trials**)

The investigators will register the information in the CRF, describing their nature (local or systemic), intensity and the necessary treatment to relieve them.

According to WHO guidelines (WHO technical report series N° 850, 1995), the intensity degrees are:

0: No adverse reaction

1: Mild: it does not require treatment

2: Moderate: it requires treatment, and disappears with treatment.

3: Severe: it puts the patient's life in danger or produces the death. It requires prolonged hospitalization, produces significant or persistent disability or congenital malformations.

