## Evaluation of the viral infection markers and statistic hypothesis

**HBV-DNA:** Response: Undetectability of HBV DNA in the serum of infected patient by using a quantitative PCR assay with 250 copies/mL as a viral detection limit of sensitivity at the end of therapy with NASVAC TVC as well as in every study cut starting from dose number five and ending at one year after treatment started.

The success criteria will be assessed one year after study started however it can be evaluated for Interim Analysis according to the date of virological assessment.

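### A severe adverse event ends trial participation as well as treatment, and nothing then requires the one-year HBV DNA sample to be taken

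*Protocol*

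**What the plan says.** Four places in the protocol bear on what happens after a severe adverse event.

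- **Procedure for adverse reactions treatment (section 8):** "In case of severe AE the treatment is stopped and the patient is immediately withdrawn from the trial".
- **Section 5.5:** the heading joins exit with interruption of treatment, and the list includes "Severe adverse reactions according to WHO guidelines". The section closes with "Patients, once included, will be considered in the analysis even if they interrupt the treatment" and adds that no case report form is discarded.
- **Evaluation criteria regarding safety (section 7), on exits:** "The patients that abandon the trial will always be evaluated, except if the investigator loses contact with him". The cause of exit is recorded. No time point, visit or test is named.
- **General ethical considerations (section 3), on disease progression:** "the patient will be withdrawn from the study treatment and given a recognized specific anti-hepatitis therapy".

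The main variable is serum HBV DNA, with response defined as undetectable at a limit of 250 copies/mL. On timing, section 10 says: "The success criteria will be assessed one year after study started". Severe is grade 3 on the WHO scale: "3: Severe: it puts the patient's life in danger or produces the death". The definition also covers prolonged hospitalisation, disability and malformation.

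On tolerability, the rationale says "It has been widely recognized the adverse reactions of interferon therapy" and that none of these reactions has so far been linked to NASVAC. The working hypothesis expects fewer adverse reactions with NASVAC. No severe-event rate is given for either arm.

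**The concern.** Stopping treatment and leaving the trial are different events. The severe-event rule orders both, so a patient can be in the analysis set under section 5.5 and yet have no one-year HBV DNA. How missing values are handled can be left to an analysis plan. Whether the sample is drawn is a protocol instruction.

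The gap may not be equal between arms. The protocol expects more reactions on interferon. Its visit table ends NASVAC treatment at week 24 and interferon at week 48, so interferon patients are on treatment about twice as long before the one-year assessment. The trial is open, so severity and withdrawal are judged with the arm known. Missing outcomes that depend on toxicity, and through it on arm, would then enter the comparison on which success is decided.

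**Working it through.** **Step 1. Does the text require the one-year sample after a severe event?**

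| Place | What ends | What continues |
|---|---|---|
| Section 8, severe event | Treatment and trial participation | Not stated |
| Section 5.5 | Exit or interruption, not distinguished | Inclusion in the analysis |
| Section 7, exits | Trial participation | An evaluation, with no time and no test named |
| Section 3, progression | Study treatment | Not stated, but the trial is not said to end |

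One evaluation on the day of exit would satisfy section 7. Nothing obliges the site to draw HBV DNA at one year. Nothing forbids it either. The outcome may therefore go uncollected; the text does not say that it will.

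**Step 2. How large could the effect be?** The protocol has no figure to reproduce, so this is an illustration. Let w be the fraction of an arm withdrawn, p the response rate among those retained, and q the rate that the withdrawn patients would have shown at one year, taken as equal in both arms.

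- Rate with full follow-up: (1 − w)p + wq
- Rate with withdrawn patients counted as failures: (1 − w)p
- Fall within an arm: wq
- Rise in the NASVAC-minus-interferon difference: (w_interferon − w_NASVAC) × q

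Assumed inputs: an excess withdrawal on interferon of 1 to 5 percentage points, and q = 0.30. The value of q borrows the efficacy of around 30% that section 2.4 gives for current treatments on some criteria. That figure is not specific to this endpoint.

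- Low: 0.01 × 0.30 = 0.003, or 0.3 points
- High: 0.05 × 0.30 = 0.015, or 1.5 points

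With 80 patients per arm, as in the design section, this excess is 0.8 to 4 patients.

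**Step 3. How does the result depend on the assumptions?** Take response among retained patients as 0.50 on NASVAC and 0.30 on interferon (assumed). The complete-case difference is then 0.200 throughout.

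| Withdrawn, interferon vs NASVAC (assumed) | Patients of 80 | Counted as failures | Full follow-up if none of the withdrawn would respond | Full follow-up if all would respond |
|---|---|---|---|---|
| 2% vs 0% | 1.6 vs 0 | 0.206 | 0.206 | 0.186 |
| 5% vs 1% | 4.0 vs 0.8 | 0.210 | 0.210 | 0.170 |
| 10% vs 2% | 8.0 vs 1.6 | 0.220 | 0.220 | 0.140 |
| 15% vs 2% | 12.0 vs 1.6 | 0.235 | 0.235 | 0.105 |

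For the third row, counting as failures gives 0.98 × 0.50 − 0.90 × 0.30 = 0.490 − 0.270 = 0.220. If all withdrawn patients would respond, it is (0.490 + 0.020) − (0.270 + 0.100) = 0.140. The gap between complete-case and full follow-up runs from 0.6 points (2% vs 0%, none responding) to 9.5 points (15% vs 2%, all responding). The upper end needs both a high rate of grade 3 events and universal response among those withdrawn.

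**The case against.** The other side has several good points, and most of them limit the concern without removing it.

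- **The exit paragraph says patients who leave are always evaluated.** It sets no single-visit limit, so a reader who infers that one-year HBV DNA is lost goes beyond the text. What stands is that the paragraph does not require that sample.
- **The analysis rule and the withdrawal rule might be read as a flat contradiction.** They are not. One governs who is analysed and the other governs conduct, and a withdrawn patient can still be counted, for example as a non-responder. They are in tension.
- **Counting such a patient as a failure is a legitimate definition of response.** It distorts the comparison only if the target is response regardless of stopping treatment, which the protocol does not state. It should still be a choice, and not one forced by uncollected data.
- **Severe means grade 3, so numbers may be small.** The passages on interferon speak of adverse reactions in general. Larger shifts can be computed, such as 0.15 × 0.60 = 0.09, but neither input has a source in the protocol, and the product is the shift in the between-arm difference, not the fall in the interferon rate.
- **The direction of total loss is not certain.** One exit criterion in section 5.5, fever or infection that suspends three vaccine administrations, can apply only to NASVAC.
- **A reader might infer that safety follow-up of the worst cases ceases.** The documents do not support this. Notification of a severe event must include its evolution, and investigators must provide care to patients who leave.
- **Continued sampling has its own problem.** The ethics section lets patients in either arm who do not control the viral load receive antivirals, so a late HBV DNA result may reflect another therapy. Deaths cannot be followed under any wording.

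**Conclusion.** The point holds in a limited form. The severe-event rule ends trial participation as well as treatment, sits badly with sections 3 and 5.5, and is not repaired by the exit paragraph. The main outcome may therefore go uncollected for these patients, probably more often on interferon.

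The size cannot be derived from the protocol. On an assumed excess withdrawal of 1 to 5 points and 30% response among those withdrawn, counting them as failures shifts the between-arm difference by 0.3 to 1.5 points in favour of NASVAC, against a margin of 20. Larger effects need higher assumed rates. The likely effect is small, but data that are not collected cannot be recovered and the correction is cheap, so the change is worth making.

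**What to change.** Leave the rule for stopping treatment as it is. Reconcile sections 3, 5.5, 7 and 8 on what follows:

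1. State that a severe adverse event ends study treatment, and that scheduled visits with HBV DNA, serology and ALT continue through one year unless the patient withdraws consent or dies.
2. In section 5.5, separate the reasons that interrupt treatment from those that end follow-up.
3. In the exit paragraph of section 7, name the tests and time points that the evaluation covers.
4. Record any antiviral therapy started after study treatment ends, with its date, so that the one-year HBV DNA can be interpreted.

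The cost is a wording change, one more item on the case report form, and a few already-scheduled visits for a small number of patients.

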### **Notification of adverse events (AE)**

Severe AE will be notified to the main investigator and the monitors immediately or before 72 hours after apparition. If a death occurs it will be notified to the monitors before 24 hours of having happened.

Notification should include:

- General data of the patient (group of treatment, age, sex, code number)
- Date of AE, description.
- Treatment applied
- Evolution

## 9. Data management

### Procedures

| FORMS                                                                     | MOMENT TO FILL                          | INFORMATION COLLECTED                                                               | RESPONSIBLE                             |
|---------------------------------------------------------------------------|-----------------------------------------|-------------------------------------------------------------------------------------|-----------------------------------------|
| Annex 1. Informed Consent                                                 | Before each patient's inclusion         | Patient's, family or legal guardians consents                                       | Responsible investigator in the service |
| Annex 2. Case Report Form and Compliance Control                          | At the beginning and at each evaluation | General data, clinical, laboratory, evolution and final evaluations of each patient | Specialist that evaluates               |
| Annex 3A and 3B. Case Report Form for Adverse Events                      | After each dose                         | AE                                                                                  | Specialist that evaluates               |
| Annex 4. Instructive for filling out the adverse events case report form. | Not to be filled                        | -                                                                                   | -                                       |
| Annex 5 Scale of adverse events                                           | Not to be filled                        | -                                                                                   | -                                       |
| Annex 6A and 6B. Record of the medicine administration.                   | At each application                     | Medication administered                                                             | Nurse that administers or patient       |

|                                                                                                                    |                                                     |                                                                                                |                                               |
|--------------------------------------------------------------------------------------------------------------------|-----------------------------------------------------|------------------------------------------------------------------------------------------------|-----------------------------------------------|
| Annex 7:
Verification of
inclusion and
exclusion criteria
before the
administration of
each dose | At each application                                 | To verify criteria                                                                             | Responsible
investigator in the
service |
| Annex 8: Model of
initial screening                                                                             | During the whole
period of inclusion
of cases | Lists of patients with diagnosis that
go to the service and if they were
included or not | Responsible
investigator in the
service |
| Annex 9 List on
included
volunteers                                                                          | After the inclusion
process                      | Lists of patients finally included in
the trial                                             | Responsible
investigator in the
service |

The clinical investigator will fill the Case Report Form (CRF) clearly and in a readable form, preferably with black ink and duplicate. The procedure appears in each CRF.

The original forms will be picked up during the visits to the institution, once complete; the duplicate will be kept by the investigator in the trial file. The primary information should be kept in the hospital during the period of time established by the authorities.

Each form should contain the subject's identification code, conformed by the inclusion number and the institution code (listing of codes appears in each CRF).

At the bottom of each model a space appears to consign the doctor's name that filled model as well as the date.

The data will be introduced in two duplicate databases by two different operators and in different computers. An application made in FOXPRO will be used. Once completed, these bases are compared in order to detect errors. The process will be repeated until no errors appear (both databases are identical).

Once be the base free of errors will be applied a program of cleaning to determine and to rectify inconsistent responses that have not been detected in the entrance of data process.

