Further clinical research is required as in case the concept of therapeutic immunization is probed, a large amount of world population will find in therapeutic vaccination a new finite and affordable treatment to overcome current situation.

*All previously presented facts induced the following **working hypothesis**:*

*The administration of NASVAC to CHB patients may subvert tolerance to the surface and core antigens (Ag) of HBV inducing specific immune responses (antibody seroconversion to anti-HBs and anti-HBe), T cells (Th1, CTL) and antigen presenting cells (APCs). Such immune response will favor the control of virus replication and will normalize the transaminases (ALT and AST) in a similar or superior extent to the currently approved treatment Interferon alpha 2b, associated to a lower number of adverse reactions.*

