### **Design of the trial**

The population sample to be tested will be of 160 CHB patients, with variable serum transaminase levels, without treatment for at least 6 months, selected according to inclusion and exclusion criteria and allocated in two study groups (SG). The first study group, SG1 will include 80 CHB patients (HBeAg (+) and HBeAg (-)) that will be treated with 1 mL NASVAC (100 mcg per antigen, per dose per patient), administered in two cycles of inoculations, the first one by the intranasal route with five intranasal inoculations every 14 days each. During the second cycle patients will receive the same dosis (100 mcg per antigen) by the intranasal route and additionally the same dosis by the SC route,

The SG2 will be treated with Alpha-Interferon at standard dosis (weekly injection by SC route).

The treatment is discontinued for all patients of SG1 after completion of both cycles. The evaluation will continue during one year, but an interim report will be released after 5 and 10 administrations.

During the whole treatment period up to one year from the beginning of treatment, the systematic assessment of patients is launched to determine to what extent the treatment has driven them to generate the capacity to control the HBV load. This information is included in Figure 1.

[figure not shown]

**Figure 1.** General Algorithm of the trial

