### Treatment schedule

The NASVAC TVC will be administered **to SG1** during the first cycle in a final volume of 1.0 mL (100µg of HBsAg and 100µg of HBcAg) by intranasal route with 8 actuations of 125 µL until completing . The second cycle will continue the IN administration in the same dosis and frequency and simultaneously the same treatment will be administered by the SC route. The device to be used (Valois VP7D spray pump) will be actuated with five minutes intervals between actuations in the same nostril.

The pegylated IFN will be administered **to SG2** weekly by subcutaneous route in the established dose (180µg) .

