#### **Adverse events (AE)**

To build a table with the frequency of AE per patient for each presented, as well as their severity, to studying which are the most frequent AE.

To study the relationship with the control variables and the appearance of each adverse reaction through a logistic regression analysis where the importance of each variable is obtained in the response prediction and the ratio of probability and conditional probabilities of response for each category of the qualitative variables and for the desired increments of the quantitative variables are estimated.

To compare both treatment groups considering the frequency of AE. For this purpose the chi-square test will be used. In case of quantitative variables that measure the intensity of a reaction, such as fever, blood pressure, ALT increase, etc. the Student's t test will be used, when possible. Otherwise, non parametric tests will be used. Paired tests will be used for the comparison between products and between periods of treatment.

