## **11. Practicalities**

### **Detailed plan. Subject management**

Patients from the Gastroenterology outpatient consultation potentially can participate in the protocol. These sessions should take place at least once per week and the following steps will be taken with every patient that fulfills the inclusion criteria:

- Clinical examination by specialists.
- Laboratory analyses
- If the patient fulfills the rest of the inclusion criteria and does not have any of the exclusion criteria, his written consent is requested after the proper explanation.
- The individual data form will be filled.
- The patient will receive an explanation about the treatment and its time of duration.
- The day before the beginning of treatment, serum samples will be taken for the baseline data.
- The injections will take place every fortnight at the clinic. Clinical examinations will be done according to the established schedule.
- At each evaluative consultation the appointment for the next one will be established.

For the purpose of quantitative HBV-DNA determinations, the serum samples will be taken at the consultations and kept frozen until their transportation to laboratory. HBV-DNA determination for inclusion will be the same method to the one to be used during assay.

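### Adverse event collection rules conflict and differ between the arms, and the chi-square comparison has no common window or patient-time

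*Protocol*

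**What the plan says.** Section 9 (Procedures) lists the adverse event form, "Annex 3A and 3B. Case Report Form for Adverse Events", as filled "After each dose" by the evaluating specialist. It gives no arm-specific rule. The general case report form is filled at the start and at each evaluation.

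Dosing differs between the arms. For the vaccine, section 4 describes two cycles, "the first one by the intranasal route with five intranasal inoculations every 14 days each", and section 6 adds "The second cycle will continue the IN administration in the same dosis and frequency". The interim analysis text refers to 5 and 10 administrations, and the test calendar places the end of vaccine treatment at week 24. Interferon is weekly (section 6), the resource table in section 12 counts 48 units over 48 weeks, and the calendar ends interferon treatment at week 48.

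Section 7 (Evaluation criteria regarding safety) gives a different collection rule. All adverse events during the study go into the case report form, and observations other than the first-hour ones are assessed at follow-up visits 14 days apart. It does not say which arm these visits apply to or when they end. The immediate observation covers "All medical incidents that occur in the first hour after each administration of the vaccine, causally related or not". A note after the test calendar adds ALT and AST after each vaccine dose, in that group only.

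Section 11 says "The injections will take place every fortnight at the clinic", without separating the arms.

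The analysis in section 10 is "To compare both treatment groups considering the frequency of AE. For this purpose the chi-square test will be used", following a table of event frequency per patient. The working hypothesis at the end of section 2.7 expects the vaccine effect to be "associated to a lower number of adverse reactions" than with interferon.

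**The concern.** A comparison of the proportion of patients with an adverse event is interpretable only if both arms are asked in the same way over the same time, or if the analysis allows for the difference. The protocol secures neither.

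Read alone, section 9 follows interferon patients with event forms for roughly twice as long as vaccine patients. Read alone, section 7 could give a common 14-day calendar, but its arm and end date are open, and 14 days is also the vaccine dosing interval. Two sites could follow the protocol faithfully and collect different data.

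The one-hour observation and the extra transaminase tests are further differences, this time towards more detection on vaccine. The claim at stake is the favourable safety profile against interferon. It is not part of the formal hypotheses, but it is one of the stated reasons for the trial.

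**Working it through.** **Dosing occasions, checked against the resource table.** Interferon: 1 per week × 48 weeks = 48 units, as listed. Vaccine at 0.5 mL per unit and 1 mL per route: 5 intranasal doses × 2 units + 5 combined doses × 4 units = 30 units, as listed. So there are 10 vaccine dosing occasions. At 14-day spacing they cover 10 × 2 = 20 weeks, or 24 weeks if collection runs to the calendar's end of vaccine treatment.

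**Collection rules side by side.**

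| Item | Vaccine arm | Interferon arm |
|---|---|---|
| Form after each dose (section 9) | 10 occasions, ending weeks 20–24 | weekly dosing to week 48 |
| All events, 14-day visits (section 7) | arm and end date not stated | arm and end date not stated |
| One-hour observation (section 7) | yes | not mentioned |
| ALT/AST after each dose (section 7) | yes | no |

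**Illustration.** Background events accrue with time, so I use a rate per week rather than per form. The rate *r* is not in the documents. It is assumed equal in both arms, with weeks independent. Patients per arm: 80 (section 4) or 60 (section 10). No significance level is given for adverse events, so two-sided 5% is assumed.

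Proportion with at least one event over *w* weeks = 1 − (1 − r)^w. With r = 1%:
- 20 weeks: 1 − 0.99^20 = 18.2%
- 48 weeks: 1 − 0.99^48 = 38.3%
- difference d = 0.2006; ratio of observation time 48/20 = 2.4

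Chance of a significant result ≈ Φ[(d − 1.96·SE0)/SE1], where SE0 is the pooled and SE1 the unpooled standard error:
- 60 per arm: SE0 = 0.0822, SE1 = 0.0801; (0.2006 − 0.1611)/0.0801 = 0.49, so about 69%
- 80 per arm: SE0 = 0.0712, SE1 = 0.0694; (0.2006 − 0.1396)/0.0694 = 0.88, so about 81%

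The same formulas over a range of assumptions:

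| r per week | Weeks of collection | Patients with an event | Significant, 60 to 80 per arm |
|---|---|---|---|
| 0.5% | 20 vs 48 | 9.5% vs 21.4% | 43% to 55% |
| 1% | 20 vs 48 | 18.2% vs 38.3% | 69% to 81% |
| 1% | 24 vs 48 | 21.4% vs 38.3% | 52% to 65% |
| 2% | 20 vs 48 | 33.2% vs 62.1% | 90% to 96% |
| 1% | 48 vs 48 | 38.3% vs 38.3% | about the nominal 5% |

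The last row is the position once both arms share one schedule and window.

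**The case against.** The strongest answer is that section 7 is the general rule. It requires all events in the study to be recorded, is not limited to an arm or to dosing, and sets 14-day visits, while the test calendar runs to week 96. Under that reading there need be no difference in background events at all. This stands in part: the illustration holds only if collection ends with dosing. It does not remove the point, because section 7 does not say that its visits cover both arms or continue after the tenth vaccine dose, and section 9 gives the event form a different trigger.

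A reader might infer more: that 10 against 48 forms are established, that collection alone would produce the hypothesised lower count, and that a false difference is nearly certain. Giving each form the same 1% risk does yield 9.6% against 38.3%, significant in 97% to 99% of trials. The documents do not support this reading:
- The form is completed by the evaluating specialist, whereas the administration record may be filled by the nurse or the patient. A specialist's form for each weekly interferon dose is not assured.
- A weekly form covers about half the time of a fortnightly one, so equal risk per form is the wrong model.
- The general case report form is filled at each evaluation, so it cannot be said that late vaccine-arm events have nowhere to be recorded.

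Two further objections are sound. A longer interferon course can cause real additional events, which are not an artefact. And the vaccine-only observation and transaminase tests raise detection on vaccine; section 10 names ALT increase among the reactions compared. The net direction is therefore open. The annexed forms and their filling instructions, which would show the recall period, are not at hand.

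An analysis plan may add exposure adjustment. It could not repair events that were never asked about on a common basis.

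**Conclusion.** The point holds as a conflict between sections 7 and 9, together with unequal collection between the arms and a comparison that does not allow for it. As written, the chi-square result can mix true toxicity with differences in ascertainment and length of observation, and the protocol offers no way to separate them.

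The size depends on how the conflict is read. If collection stops with dosing, a background rate of 1% per week gives 18% against 38% and a significant result in about 69% to 81% of trials. If both arms share one calendar, the expected difference is zero. These figures rest on an assumed equal and constant rate, independent weeks and a two-sided 5% level. They leave out the vaccine-only procedures, which act in the opposite direction. It should not be concluded that the plan is certain to favour the vaccine.

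**What to change.** - Reconcile sections 7 and 9: state one adverse event calendar for both arms through the end of follow-up, explicitly including the vaccine arm after the tenth dose, and the period each form covers.
- Apply the same post-dose observation rule to clinic-given doses in both arms.
- In section 10, compare adverse events per patient-time and over a common window, for example weeks 0 to 24, alongside the whole-period frequencies so that later interferon events stay visible. Identify ALT findings that come only from the extra vaccine-arm samples.
- Reconcile the fortnightly injections in section 11 with the weekly interferon in section 6. Which statement is right is for the sponsor and the investigators to settle.

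The cost is a change in form timing, some wording and one additional adverse event table.
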